## Abstract

**Introduction::**

The Kids Guided Personalised Service (KidsGPS) is an integrated model of care coordination for children and young people (CYP) living with medical complexity. After successful implementation in an urban setting, the model of care will be rolled-out at scale to four rural regions in New South Wales, Australia to establish RuralKidsGPS. This paper describes the approach and methods for the outcome and implementation evaluation of RuralKidsGPS.

**Description::**

The evaluation aims to assess health, economic and implementation outcomes and processes whilst identifying barriers and enablers to inform future rollouts. Measures of health service utilisation (primary outcome), child health related quality of life and parent/carer experiences will be assessed. The implementation evaluation will occur alongside the outcomes evaluation and is underpinned by the Consolidated Framework for Implementation Research and informed by validated quantitative measures and qualitative interviews with patients, families, healthcare providers and service managers. An economic analysis will determine incremental cost effectiveness ratios for the new model of care using health service utilisation data.

**Conclusion::**

RuralKidsGPS, if effective, has the potential to improve equity of access to integrated care for CYP and their families and this protocol may inform other evaluations of similar models of care delivered at scale.

## Introduction

Children and young people (CYP) who are medically complex have multiple and/or significant chronic health problems. This group represents approximately 10% of patients attending children’s hospitals, but accounts for 60% of expenditure [1,2]. CYP who are medically complex require support from different health care teams frequently based across more than one service and location. In the absence of planned coordinated care for these CYP, missed and/or duplicated care increases costs for the health system and out-of-pocket expenses for families [3]. The cost of uncoordinated care is estimated to be up to 35% higher than coordinated care [4].

A care coordination service for CYP with chronic and/or complex health conditions, developed at the Sydney Children’s Hospitals Network (SCHN) in Sydney, New South Wales (NSW), Australia, known as Kids Guided Personalised Service (KidsGPS) has already demonstrated successful outcomes in the metropolitan setting [3]. The service is focussed on CYP with increased care coordination needs due to several factors, including medical complexity, vulnerability, involvement of multiple health care teams, and reduced access to appropriate services. Evaluation of KidsGPS demonstrated a 40% reduction in emergency department (ED) presentations and 42% reduction in day-only admissions over 2 years for 534 CYP who had over 50 different diagnoses [3]. Through the adoption of KidsGPS, approximately $2.5 million/annum was saved for the tertiary hospital network, and >50,000 km of family travel was prevented [3]. Systematic review and meta-analyses data published by our research team have indicated that paediatric integrated care interventions significantly improve CYP related quality of life scores compared to usual care [5].

In NSW, Australia, 500,000 children, 30% of the state’s total, live outside major cities. To address the healthcare needs of this population, Rural Kids Guided Personalised Service (RuralKidsGPS) was co-designed with parents and professionals as an innovative child-centred model of care for CYP living with medical complexity in rural and remote regions. Within the RuralKidsGPS model, a new role was established in each LHD for a paediatric care coordinator responsible for facilitating care integration and establishing a circle of coordination formed by the leads from the health service, community and family [1]. The paediatric care coordinators work closely with local and tertiary care teams at SCHN, and families, to meet the CYP’s needs through the development of shared care plans and technology-enabled healthcare. Importantly, the RuralKidsGPS model of care aims to build capacity for the family and local healthcare teams.

This paper describes a research protocol aimed at evaluating the impact of RuralKidsGPS on health service utilisation, implementation outcomes, barriers and enablers to delivering RuralKidsGPS and the cost-effectiveness of this program for families and the healthcare system.

## Methodology

### Study design

The evaluation of RuralKidsGPS will consist of an integrated impact, implementation and economic evaluation embedded within a quasi-experimental study across four rural NSW local health districts (LHDs) in Southern, Northern and Western New South Wales and Murrumbidgee (Figure 1).

**Figure 1 F1:**
[figure not shown]
Local Health Districts involved in the RuralKidsGPS study.

The primary aim of this evaluation is to assess the impact of RuralKidsGPS on health service utilisation (ED presentations, hospital admissions, and outpatient (OP) appointments), among CYP enrolled in RuralKidsGPS intervention compared to usual care.

The secondary aims are to:

Describe trends in health service utilisation (ED presentations, hospital admissions, OP appointments, and general practice (GP) attendances) over time;Assess the change in parent reported satisfaction with care, parental wellbeing, and parent and CYP reported quality of life at enrolment, at 6 and 12 months after recruitment to RuralKidsGPS;Assess the implementation of RuralKidsGPS model from the perspective of families, CYP, healthcare providers, managers, and practitioners, and factors that help or hinder this implementation to inform further adaption of the model and ensure scalability;Assess the cost-effectiveness of RuralKidsGPS model of care compared with standard care.

### Ethics

This study will be guided by the RuralKidsGPS Steering and Evidence Translation Committee which includes in its membership representatives from all participating local health districts and consumers. Ethical oversite for this study is held by the SCHN Human Research Ethics Committee (2021/ETH01055).

### Study cohort

The study population includes CYP with medical complexity aged 0 to 18 years, referred for care coordination, who meet the following criteria:

– A diagnosis expected to last at least 12 months– And if ≥ 6months of age, frequent use of health services within the last six-month period, defined as:Two or more ED presentations, ORHospital admission for seven days or more, ORTwo or more outpatient appointments.

A cohort of CYP meeting these criteria and referred for care coordination, their parents and guardians, and clinical and non-clinical staff involved in the planning and/or delivery of the RuralKidsGPS model of care, will all form a part of the study cohort.

### Recruitment

Children meeting the inclusion criteria for care coordination as described above will be recruited within each of the four LHDs. For children enrolled into the local service, the paediatric care coordinator (PCC) will discuss with each family their potential participation in the evaluation project. After providing a brief overview of the project, the PCC will ask permission for the contact details (parent name, contact number, email, and child name) to be shared with the researcher embedded with the local team. The embedded researcher will then contact the parent/carer and provide them with the participant information sheet and consent form.

Clinical staff (e.g. healthcare providers), and non-clinical staff (e.g. service managers) involved in the care coordination of the children will be recruited from each of the four LHDs and SCHN. Members of the research team will make direct contact with clinical and non-clinical staff and will provide them with an information sheet and consent form which describes what is involved in the research and that participation is voluntary. Upon agreement and consent, the implementation evaluation team will organise a suitable time to conduct the interview or focus group. Links to study surveys will be sent via an invitation email including the participant information form. These forms will also will be embedded in the electronic surveys and participants will be asked to confirm that they have read these and that they consent prior to completing the survey.

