#### Impact Evaluation: Patient and family reported outcomes data collection

In our intervention cohort, secondary child and parent reported outcomes will assess family reported experiences and parental satisfaction with care integration (PICS) [6], out of pocket expenses (adapted Mumford Scale) [7], parent and child quality of life (EQ5D5L) [8], (PedsQL4.0) [9], (CHU9D) [10] and parental wellbeing (WEMWBS) [11]. These measures and basic demographic data (e.g. date of birth, postcode for estimation of Indexes of Relative Advantage and Disadvantage [12], gender, Aboriginal and Torres Strait Islander Status) will be collected via phone and secure electronic survey by a researcher embedded in each of the LHDs, at three time points: enrolment, 6 months and 12 months later to enable longitudinal comparisons, (Table 1).

**Table 1 T1:** Family reported outcome measures.

OUTCOME MEASURES	PURPOSE

Paediatric Integrated Care Survey (PICS) [6]	Measures experiences of integration of child’s care

Adapted Mumford scale [7]	Measuring non-medical out of pocket expenses for families

EuroQol 5 Dimension 5 Level (EQ-5D-5L) [8]	Health status measure

Paediatric Quality of Life Measure (PedsQL4.0) [9]	Measuring health paediatric health outcomes

Child Health Utility 9D (CHU 9D) [10]	Instrument used to adjust quality of life years from PedsQL4.0 score for economic evaluation

Warwick-Edinburgh Mental Well-being Scale (WEMWBS) [11]	Understanding and measuring mental health and wellbeing

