#### Impact Evaluation Analyses

Based on local data from the participating LHDs, we aim to recruit 400 children across the four LHDs. We will match each case by 20 controls, resulting in a total of 8,000 controls. This will provide 90% power to detect a 20% difference in the number of health service use occasions, including outpatient visits and hospital admissions between intervention and comparison groups. Having 400 cases will also provide the power of 90% to detect a within-group 20% decrease in the number of health service use occasions. This sample size will also allow us to detect a clinically important difference (4.36 points) for child health related quality of life in children post- vs pre-intervention change in the PedsQL4.0 Total Scale Score [9].

We will calculate rate of health service use (e.g. ED, hospital admissions and OP visits) in person-years for the intervention and comparison groups during the baseline (3 years prior to enrolment) and the intervention period (12 months after enrolment), respectively. To assess the effectiveness of this intervention, we will conduct multivariable Poisson (negative binomial if over-dispersion is present) regression analysis with intervention status (intervention versus comparison) as the main independent variable and the rate of health service use (ED, hospital admissions and OP visits, separately and combined) during the intervention period as the outcome variable.

To examine how health service use changes over time between intervention and comparison groups, we will analyse rates of health service use during baseline and intervention periods using mixed effect Poisson regression models, including the interaction term between intervention status and time (after RuralKidsGPS implementation versus before RuralKidsGPS). In all regression analyses, we will control for participant socio-demographics (e.g., age at enrolment, sex, Aboriginal and Torres Strait Islander status, socio-economic status) and clinical factors (e.g., type and severity of health conditions), and baseline rate of health service use. Considering potential clustering effect by site, we will use the generalised estimating equations (GEE) approach in the regression analysis.

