**Figure 4 F4:**
[figure not shown]
Using interrupted time series analysis to measure change before and after intervention. Adapted from Kontopantelis et al 2015 [13].

Regarding patient and family reported outcomes, we will describe them at each survey time point using mean and standard deviation, or median and inter-quartile range. We will conduct regression analysis of these outcomes at each survey (pre-intervention, 6-month and 12-month post-intervention), respectively, with intervention status as the main independent variable. We will control for participants’ socio-demographic, clinical and baseline outcome variables, and use the GEE approach to account for potential clustering effect by site. We will conduct intention-to-treat analysis.

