Outcome data will capture changes to parent and child reported quality of life assessed using the validated instruments EQ5D5L15 (parent) [8] and Paediatric Quality of Life Inventory (PedsQL4.0), and Child Health Utility 9D (CHU9D) [10] (internal consistency 𝛼 = 0.89 children and 0.92 parent report). These utilities will be included in the estimation of QALYs (quality-adjusted life-years) by calculating the area under the curve, assuming a linear change between the survey dates. QALYs calculated for the year before the intervention starts are based on the health state utility measured at baseline, which was assumed to be stable during the year before.

Cost-effectiveness will be expressed as incremental change in costs (measured by ED presentations, hospital admissions, or OP visits averted), and cost-utility by changes in QALYs gained. Cost-effectiveness will be measured between pre and post implementation of the intervention and calculated according to the formulas below:

\[\begin{array}{l}
Effect\ differences:\ \Delta QALYs = QALY{s_{post\ new\ model\ of\ care}} - QALY{s_{pre\ new\ model\ of\ care}}
\end{array}\]

\[\begin{array}{l}
Cost\ differences:\ \Delta Total\ costs = Total\ cost{s_{postnew\ model\ of\ care}} - Total\ cost{s_{pre\ new\ model\ of\ care}}
\end{array}\]

Imputation methods will be applied to missing values and sensitivity analyses will be conducted for key cost parameters in the data sets to ensure the robustness of the estimates. An additional bootstrap analysis with random 1,000-fold resampling of the original population will be conducted to ensure the validity of confidence intervals.

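### The first family survey follows service entry by an unlimited lag, yet it serves as the pre-intervention value for the survey outcomes and the QALY difference

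*Protocol article*

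**What the plan says.** All places are in the protocol article.

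- **Recruitment.** The approach starts with a child already in the service: "For children enrolled into the local service, the paediatric care coordinator (PCC) will discuss with each family their potential participation in the evaluation project". The coordinator asks permission to pass on contact details, and then: "The embedded researcher will then contact the parent/carer and provide them with the participant information sheet and consent form".
- **Patient and family reported outcomes data collection.** The embedded researcher collects the surveys, in the intervention cohort, "at three time points: enrolment, 6 months and 12 months later to enable longitudinal comparisons".
- **Study design, secondary aims.** The survey measures are assessed "at enrolment, at 6 and 12 months after recruitment to RuralKidsGPS".
- **Impact Evaluation Analyses, paragraph on family reported outcomes.** The plan is a "regression analysis of these outcomes at each survey (pre-intervention, 6-month and 12-month post-intervention), respectively". The first survey is therefore the pre-intervention one. The same paragraph states an intention-to-treat analysis.
- **Economic evaluation.** "QALYs calculated for the year before the intervention starts are based on the health state utility measured at baseline", with utility assumed stable over that year. The post-intervention year is an area under the curve, linear between surveys.
- **Impact Evaluation Analyses, health service use.** Rates are calculated "during the baseline (3 years prior to enrolment) and the intervention period (12 months after enrolment", from linked administrative records.
- **Implementation evaluation quantitative data collection.** Child data are said to be gathered both before and after enrolment in the care-coordination model. Table 3 places the family PICS survey at baseline, which it equates with enrolment.

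**The concern.** The stated order is service enrolment, coordinator approach, researcher contact, consent, first survey. The coordinator who raises the evaluation also delivers the intervention, and the first task listed under Intervention is to understand the family's needs. Followed as written, a site takes the first survey after service entry and after at least one coordinator contact. The delay is not bounded and can differ between the four districts.

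This matters because the first survey is the whole reference for the survey outcomes. The article describes surveys only in the intervention cohort, and its cost-utility formula is post minus pre. The analysis paragraph does name intervention status as a regressor, but no surveyed comparison families are described, so nothing removes a shift already present at the first survey. PICS is the most exposed measure, since it asks about care integration, which is what the coordinator works on.

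**Working it through.** **1. What depends on the survey date**

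| Quantity | Source | Depends on date of first survey? |
|---|---|---|
| ED, admission and outpatient rates (primary outcome) | Linked records, dated from enrolment | No, if enrolment means service entry |
| Health-service costs | Linked records and unit costs | No, on the same condition |
| PICS, PedsQL, CHU9D, EQ-5D-5L, WEMWBS change | Surveys | Yes |
| QALY difference | Survey utilities | Yes, in both the pre and post terms |

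**2. The QALY rule**

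Let u_b, u_6 and u_12 be utility at the first, 6-month and 12-month surveys.

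- Pre-year QALYs = u_b
- Post-year QALYs = 0.5(u_b + u_6)/2 + 0.5(u_6 + u_12)/2 = 0.25u_b + 0.5u_6 + 0.25u_12
- Difference = 0.5u_6 + 0.25u_12 - 0.75u_b

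If u_b already contains a shift c, the pre-year rises by c and the post-year by 0.25c. The two entries partly cancel, and the net error is -0.75c.

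Illustration A (assumed utilities 0.70, 0.74, 0.76):

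- No shift: 0.37 + 0.19 - 0.525 = 0.035
- First survey at 0.72 (c = 0.02): 0.37 + 0.19 - 0.54 = 0.020
- Loss 0.015 = 0.75 × 0.02, or 43% of 0.035. This assumes that half of the six-month gain came before the first survey.

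Illustration B (assumed gain of 0.05, reached by 6 months and held). With no shift the difference is 0.75 × 0.05 = 0.0375. With 10%, 25% or 50% of the gain already present it is 0.0338, 0.0281 or 0.0188, so the same share of the gain is lost.

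**3. PedsQL change**

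The article says that 400 children allow detection of a 4.36-point change. It gives no SD of change or alpha, so the statement cannot be reproduced. Assuming two-sided alpha 0.05 and 90% power, it holds if the SD of change is at most 4.36 × √400 / (1.960 + 1.282) = 26.9.

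If a share f of the change precedes the first survey, 4.36(1 - f) remains, and power = Φ(4.36(1 - f)/(SD/√400) - 1.96):

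| Assumed SD of change | f = 0 (4.36) | f = 10% (3.92) | f = 25% (3.27) | f = 50% (2.18) |
|---|---|---|---|---|
| 15 | >0.99 | >0.99 | 0.99 | 0.83 |
| 20 | 0.99 | 0.98 | 0.91 | 0.59 |
| 25 | 0.94 | 0.88 | 0.74 | 0.42 |

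**4. If consent, not service entry, were time zero for the linked data**

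With an assumed 3-month lag, 3 of 36 baseline months (8.3%) would be treated time. If use in those months were 20% lower, the baseline rate would be (33 + 3 × 0.8)/36 = 35.4/36 = 0.983 of its true value, and a within-group ratio of 0.80 would read 0.80/0.983 = 0.81. The first three months of exposure would also fall outside the intervention year. Even on this reading the distortion of the baseline rate is small.

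**The case against.** The strongest reply is that the article dates the first survey at enrolment, and that its implementation section speaks of data before and after enrolment. A talk about the evaluation and permission to share contact details is not care coordination. A survey done promptly, before any shared care plan operates, could carry little or no effect. Survey windows are also the kind of detail that a condensed article may leave to a fuller document.

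Much of this stands. That the first survey is taken under treatment is an inference a reader might draw, not something the article states. What remains is an order of events that the article does state, which conflicts with the pre-intervention label unless the gap is negligible. The before-and-after sentence does not settle it, because no survey earlier than enrolment is scheduled and the sentence may refer to linked records.

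A reader might also infer that every before/after comparison, including the primary outcome, starts from the wrong point. The documents do not support that. Health service use and health-service costs come from linked records. The article ties enrolment to the service and the care-coordination model, and nowhere dates the linked-data periods from consent. The main effectiveness model also uses the intervention-period rate as its outcome, with the baseline rate only as a covariate.

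Finally, a late baseline need not hide real benefit. Children aged six months or more qualify through frequent service use in the preceding six months, so some improvement after referral may be regression to the mean. A later first survey could remove part of that spurious gain.

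**Conclusion.** The point holds for the survey outcomes and the QALY difference. The recruitment order puts the first survey after service entry, with no bound on the lag and no rule that it precede care-coordination activity, while the analysis and economic sections treat it as the untreated state. The QALY error is exactly -0.75c under the article's own rule. A shift in any survey score before the first survey is lost in full from its before/after change.

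The size is unknown: the article gives neither the lag nor c, and every figure above that uses them is an illustration. With no early shift the error is zero. The net direction is also open, because early benefit and regression to the mean pull opposite ways relative to the true effect. The primary outcome and health-service costs are not affected provided time zero is service enrolment, which the article suggests but does not state outright.

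**What to change.** - Ask for contact permission at referral or intake. Complete consent and the first survey before care planning begins, or within a short stated window, without delaying care.
- State that service enrolment is the single time zero for surveys, linked-data periods and costs, and bring the recruitment, survey-timing, analysis and economic sections into line with it.
- Record and report, by district, the days from service enrolment and from first coordinator activity to the first survey.
- Keep all families in the main analysis. Add a sensitivity analysis that excludes late baselines or adjusts for the lag. Dropping late families from the main comparison would sit badly with the stated intention-to-treat analysis and could select by district if the lag varies between sites.

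The cost is a small change to the recruitment workflow, added date fields, and some families surveyed at a busy time. Baselines already taken late cannot be recovered, so the change is worth most if made early.
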